#### 2.1.4.1 Adverse events variables

The following adverse events (AE) are to be collected during the study:

- Serious AEs,
- Unexpected AEs that may be related to study procedures,
- AEs that occurred while under the supervision of guidance of study related personnel
- AE of special interest (AESI)

#### *Adverse event observation period:*

AEs are classified into three distinct categories:

- Pre-emergent adverse events are adverse events that occurred from the signed informed consent date up to the randomization visit V1-T0 or date of randomization if V1 is missing (included)
- Emergent adverse events (EAE) are adverse events that occurred from the randomization visit V1-T0 or date of randomization if V1 is missing (excluded) up to the end date of study participation (included)
- Post-emergent adverse events are adverse events that occurred after the end date of study participation

All adverse events are coded to a lower-level term (LLT), preferred term (PT), high-level term (HLT), high-level group term (HLGT), and associated primary system organ class (SOC) using the version of Medical Dictionary for Regulatory Activities (MedDRA) currently in effect at Sanofi at the time of database lock.

In SPRINTT study, SAEs criteria include the following events:

- Death,
- In-patient hospitalization
- Life threatening illness or accident,

- Permanent disability or incapacity
- Other serious illness that might have results in an SAE without aggressive medical intervention

AEs that occurred while under the supervision or guidance of study related personnel include:

- AE that meets criteria for SAE
- Event requiring active intervention by research staff to reduce potential harm
- Chest pain for more than two minutes after stopping exercise
- Dyspnea for more than two minutes after stopping exercise
- Vital signs out of range (systolic BP  $\geq 250$  mmHg or diastolic  $\geq 115$  mmHg, HR  $>120$  beats/minute or  $< 45$  beats/minute) for more than two minutes after stopping exercise
- A fall during study recommended activity
- A symptom or illness that developed and required medical management or attention

Adverse events of special interest include:

- Emergency room or urgent care visit
- Fracture
- Outpatient surgery
- Abnormal laboratory or diagnostic test result requiring immediate medical attention
- Restricted activity due to health problem potentially related to the study activity that led an inability to leave home for at least one week

#### **2.1.4.2 Falls**

Falls will be described using information collected in the Outcome events eCRF form:

- Since the last visit, participants who broke a bone as a result of a fall (Yes/No/Refused/Don't know)
- Since the last visit, participants who fallen, and participants who fallen resulting in an inability to leave home for at least one week (Yes/No/Refused/Don't know)

Injury falls will be identified using a customized MedDRA searches

### **2.1.4.3 Deaths**

The deaths observation period is from the date of randomization until the end of the study participation.

The safety endpoint mortality will also be assessed using the time from randomization to the date of death, as reported in an adverse event form by the investigator.

Participants not dead or lost to follow-up at the end of the study will be censored at the date of the study end or date of last news reported in the end-of-study form.

### **2.1.4.4 Laboratory safety variables**

Clinical laboratory data consists of blood analysis, including hematology, clinical chemistry, and urinalysis.

Blood samples for clinical laboratories will be taken at randomization visit V1-T0, M12, M24, M36 and, if applicable, at the end-of-study visit. The laboratory parameters will be classified as follows:

- Hematology
  - **Red blood cells and platelets and coagulation:** hemoglobin, hematocrit, Ery. mean corpuscular volume, Ery. mean corpuscular hemoglobin concentration, Ery. mean corpuscular hemoglobin, red blood cells count, platelet count.
  - **White blood cells:** white blood cells count, neutrophils, lymphocytes, monocytes, basophils, eosinophils
- Clinical chemistry
  - **Metabolism:** glucose, total cholesterol, HDL-cholesterol, LDL-cholesterol, triglycerides, total protein, albumin,
  - **Electrolytes:** sodium, potassium, calcium
  - **Renal function:** creatinine, blood urea nitrogen
  - **Liver function:** alanine aminotransferase (ALT), aspartate aminotransferase (AST), total bilirubin
  - **Vitamin D concentration**

### **2.1.4.5 Vital signs variables**

Vital signs include: heart rate (bpm), sitting systolic and diastolic blood pressure (mmHg) are recorded at screening, M3, M6, M12, M18, M24, M30, M36 and at the end of the study (if no evaluation in the past 3 months).

### **2.1.5 Quality-of-life endpoints**

In SPRINTT, participants' quality of life will be assessed at each clinical visit using the EuroQoL-5D instrument. The EuroQoL-5D is a 5-item questionnaire exploring the following dimensions: Mobility capacity, Self-care, Usual activities, Pain/Discomfort, Anxiety/Depression.

Each item can take one out of five possible degrees of impairment/severity and are coded from '1': no problems to '5': extreme problems. The EuroQoL-5D index utility score is calculated using the crosswalk method based on the UK value set (4).

The EuroQoL instrument also includes a 10-cm long visual analogue scale (VAS). Participants will thus be asked to draw a line from a box to the point on the thermometer-like scale (ranging from 0 [worst quality of life] to 100 [best quality of life]) "corresponding to their health-related quality of life".

### **2.1.6 Health economic endpoints**

Health economic components and analyses, including cost-effectiveness analysis, will be detailed in a separate dedicated document.

### **2.1.7 Biomarker endpoints**

Biomarkers endpoints and analyses will be detailed in a separate dedicated document.

## **2.2 DISPOSITION OF PARTICIPANTS**

This section describes participant disposition for both participant study status and the analysis populations.

Screened participants are defined as any participant who signed the informed consent.

Randomized participants consist of all participants with a signed informed consent form and who have been randomized by the system in one of the intervention arms, whatever the intervention attendance.

For participant study status, the total number of participants in each of the following categories will be presented in the clinical study report using a flowchart diagram or summary table:

- Screened participants
- Screen failure participants and reasons for screen failure as reported by the investigators in the inclusion criteria and exclusion criteria e-CRF pages
- Randomized participants
- Participants who completed the study (i.e. participants who were followed for at least 2 years)

- Participants who did not complete the study (i.e. participants who were followed for less than 2 years)
- Participants who discontinued study by main reason for study discontinuation

All categories of participants (except for the screened and nonrandomized categories) will be presented by intervention arm and the percentages will be calculated using the number of randomized participants within each intervention arm as the denominator. Reasons for study discontinuation will be supplied in a table giving numbers and percentages by intervention arm, as well as, displayed in a listing.

A summary of the distribution of participants by country and site will also be provided (overall number of patients screened, randomized, as well as number of participants who discontinued from study).

All critical or major deviations will be summarized in tables giving numbers and percentages of deviations by intervention arm.

Additionally, the following analysis study populations will be summarized by intervention arm.

- All randomized participants
- All randomized participants with a baseline SPPB score  $<8$  assigned by randomization
- All randomized participants with a baseline SPPB score  $\geq 8$  assigned by randomization

The discrepancy between randomization strata assigned by randomization (i.e. the baseline SPPB score and the sex) and the information reported on e-CRF will be summarized for all randomized patients

## **2.3 ANALYSIS POPULATIONS**

The randomized population includes any participant who has been allocated to a randomized programme whatever the number of intervention attendance.

For any participant randomized more than once, only the data associated with the first randomization will be used in any analysis population. The safety experience associated with any later randomization will be assessed separately.

The main analysis population for all analyses (i.e. efficacy, safety and quality-of-life) will be the randomized population with a baseline SPPB score  $< 8$  as assigned by randomization. Participants will be analyzed according to the intervention arm allocated by randomization.

The secondary analysis population will include all randomized participants with a baseline SPPB score  $\geq 8$  as assigned by randomization and analyzed according to the intervention arm allocated by randomization.

## **2.4 STATISTICAL METHODS**

### **2.4.1 Demographics and baseline characteristics**

Continuous data will be summarized using the number of available data, number of missing values, mean, standard deviation (SD), median, minimum, and maximum for each intervention arm. Categorical and ordinal data will be summarized using the number and percentage of participants in each intervention arm.

Parameters will be summarized on the randomized population analyzed in the intervention group to which they were randomized. Analyses will be provided in the randomized population according to the baseline SPPB categories ( $<8$ ,  $\geq 8$ ) assigned by randomization.

Parameters described in Section 2.1.1 will be summarized by intervention arm and overall using descriptive statistics.

Other medical/surgical history will be summarized in each intervention arm by primary SOC, HLT and PT. Events will be sorted by SOC internationally agreed order and decreasing frequency of HLT and PT based on the overall incidence of participants with a baseline SPPB  $< 8$  assigned by randomization.

P-values on demographic and baseline characteristic data will not be calculated.

No specific description of the efficacy parameters, safety parameters and quality-of-life parameters will be provided at baseline. If relevant, baseline values will be described along with each efficacy, safety or quality-of-life analysis, respectively.

### **2.4.2 Prior or concomitant medications**

The prior and concomitant medications will be presented for the randomized population. Analyses will be provided in the randomized population according to the baseline SPPB categories ( $<8$ ,  $\geq 8$ ) assigned by randomization.

The number of participants who reported at least one ATC coded medication (prior and concomitant separately), as well as the number of participants who reported at least one non-ATC coded medication (prior and concomitant separately) will be presented.

ATC coded medications will be summarized by intervention arm according to the WHO-DD dictionary, considering the first digit of the anatomic category (ATC) class (anatomic category) and the first 3 digits of the ATC class (therapeutic category).

All ATC codes corresponding to a medication will be summarized, and patients will be counted once in each ATC category (anatomic or therapeutic) linked to the medication. Therefore, patients may be counted several times for the same medication

The table for prior ATC coded medications will be sorted by decreasing frequency of ATC followed by all other therapeutic classes based on the incidence of overall randomized population with a baseline SPPB score  $<8$  assigned by randomization. In case of equal frequency regarding ATCs (anatomic or therapeutic categories), alphabetical order will be used.

The tables for concomitant medications will be sorted by decreasing frequency of ATC followed by all other therapeutic classes based on the incidence in the MCI intervention group with a baseline SPPB score  $< 8$  assigned by randomization. In case of equal frequency regarding ATCs (anatomic or therapeutic categories), alphabetical order will be used.

In addition, the repartition of the participants according to the number of ATC coded medications reported at screening (i.e. prior medications), as well as the number of ATC coded medications reported post-randomization visit (i.e. concomitant medications) will be summarized by visit.

### **2.4.3 Intervention attendance and compliance**

For each participant, in both intervention arms, the number of attended sessions and the number of expected attended sessions should be reported each month for the following type of sessions:

- Center-based PA attendance (MCI group)
- Home-based PA attendance (MCI group)
- HALE attendance (HALE group)

The intervention attendance and compliance will be assessed and summarized by intervention arm in the randomized population according to the baseline SPPB categories ( $<8$ ,  $\geq 8$ ) assigned by randomization.

#### **2.4.3.1 Intervention attendance**

In the MCI intervention arm, both the center-based physical exercise attendances and the home-based physical exercise attendances will be summarized.

In the HALE intervention arm, the number of sessions attended will be summarized.

For each type of sessions, the number of participants who attended at least one session, the total number of sessions attended (quantitative), and the total number of sessions per months (quantitative) will be described.

The total number of sessions attended per month will be derived as follows:

$$\frac{\text{Total Number of sessions done since the beginning of the study}}{\text{Number of months}}$$

### **2.4.3.2 Compliance**

In the MCI intervention arm, both the center-based physical exercise compliance and the home-based physical exercise compliance will be summarized.

In the HALE intervention arm, compliance will be summarized.

For each type of sessions, the compliance will be calculated per participant according to the information recorded by investigators in the e-CRF page as follows:

$$\frac{\text{Total Number of sessions attended since the beginning of the study}}{\text{Total Number of sessions expected since the beginning of the study}} \times 100$$

In addition to the attendance compliance for the MCI group, the collection of a 3-day dietary record (Y/N) will be summarized overtime.

## **2.4.4 Analyses of efficacy endpoints**

### **2.4.4.1 Analysis of primary efficacy endpoint(s)**

The analysis of the primary efficacy endpoint will be the comparison between the two intervention arms using a two-sided 0.05 alpha level log-rank test procedure stratified by randomization stratification factors (i.e., study site and gender).

The primary comparison will be conducted in the randomized participants with a baseline SPPB score <8 assigned by randomization.

The hazard ratio between intervention groups and the corresponding 95% confidence interval will be estimated using a Cox proportional hazard model stratified by the same stratification factors as those used for the log-rank test described above.

The underlying assumption of proportional hazards for Cox model will be checked graphically by plotting natural logarithm of the cumulative hazard Kaplan-Meier estimate (Log(-Log (KM survival function estimates))) versus natural logarithm of time for each intervention arm.

If proportionality is not observed on primary analysis, sensitivity analyses will be performed by including a time-dependent variable with the corresponding interaction.

The cumulative incidence functions for the 2 intervention arms will be summarized using Kaplan-Meier method and displayed graphically. The cumulative incidence rate over time at each scheduled time-points of the protocol together with appropriate 95% confidence interval will be provided.

Reason for censoring will be summarized by intervention arms.

If this primary analysis performed in the randomized population with a baseline SPPB score  $<8$  is statistically significant ( $p < 0.05$ ), the comparison will be extended to include the remaining participants with baseline SPPB 8-9 only if the interaction between the baseline SPPB randomization stratum and the intervention arm can be ignored. The hazard ratio between intervention groups and the corresponding 95% confidence interval will be then computed using a Cox proportional hazard model stratified by randomization strata (site, gender, baseline SPPB) for the comparison in the whole randomized population.

The interaction between the baseline SPPB randomization stratum and intervention arm will be assessed graphically by comparing, between the two baseline SPPB categories ( $<8$  and  $\geq 8$ ), the cumulative incidence functions for the 2 intervention arms using the Kaplan-Meier method.

### **Subgroup analyses**

The consistency of the results from the primary analysis conducted in the randomized participants with a baseline SPPB score  $<8$  assigned by randomization will be evaluated across pre-defined subgroups in patients with available results. The subgroups are:

- Gender (Female; Male)
- Race (White ; All others race)
- Age ( $<80$ ;  $\geq 80$  years)
- History of cardiovascular disease (Yes; No)
- History of diabetes (Yes; No)
- Gait speed ( $<0.8$ ;  $\geq 0.8$  m/sec)

For each subgroup, the hazard ratio and its associated 95% confidence interval will be estimated using the same Cox proportional hazards model applied for the primary analysis and by adding terms for the subgroup, intervention group and subgroup-by-intervention. A forest plot summarizing the results for each subgroup will be provided.

When the subgroup considered is equal to the randomization stratum of gender, the stratification by the randomization stratum of gender will be removed from the model.

### **Supportive analysis**

A supportive analysis will be performed by excluding deaths from the definition of the disability event (described in [Section 2.1.3.1](#)). Participants who have not met the disability criterion before to die will be considered as right-censored observations. The censoring time will be calculated as the date of their last successful completed 400-meter walk test minus the date of randomization visit V1-T0 (or date of randomization if V1 is missing) + 1 day.

Same methodology as described above in [Section 2.4.4.1](#) for the primary efficacy endpoint will be used to analyze the time (in days) from randomization visit V1-T0 (or date of randomization if V1 is missing) to the date of first occurrence of major mobility disability using the new disability definition that excludes deaths.

#### **2.4.4.2 Analyses of secondary efficacy endpoints**

The change from baseline (or percent change for weight) for all continuous variables with a normal distribution described in [Section 2.1.3.2](#) will be analyzed in the randomized population with a baseline SPPB score <8 using mixed-effect models with repeated measures (MMRM) approach. All post-baseline data available within Month 3 to Month 36 analysis window as defined in [Section 2.5.4](#) will be used.

These models will include the fixed categorical effects of intervention arm (MCI versus HALE), the planned time point (Month 3 to Month 36), the randomization strata of site and gender, the intervention-by-time point interaction as well as, the continuous fixed covariates of baseline value and baseline value-by-time point interaction. For change in body composition measures, assessed using DXA (centralized reading) (aLMBMI, and aLM), the models will be assessed separately for males and females.

These models will be run using SAS Mixed procedure with an unstructured correlation matrix to model the within-participant errors. Parameters will be estimated using restricted maximum likelihood method with the Newton-Raphson algorithm. Denominator degrees of freedom will be estimated using Satterthwaite's approximation.

These models will provide adjusted least-squares means estimates at Month 24 and Month 36 for both intervention arms, as well as the difference of these estimates, and their corresponding standard errors (SEs) and 95% confidence intervals (CI).

In addition to these models, results per time point for all planned time points visits (value at visits using analysis windows, and changes from baseline) will be summarized and plotted for all quantitative secondary endpoints using LS mean and SE for each intervention group obtained from the same MMRM models as used for endpoints above and with raw values and changes from baseline as response variable in the model as appropriate. For weight, similar summary will be provided, but the percent change from baseline will be presented instead.

Time to first occurrence of persistent mobility disability will be compared, as for the primary analysis endpoint, in the randomized population with a baseline SPPB score <8 within the intervention arm, using a two-sided Log-rank's test stratified by study site and gender. Hazard ratio (and 95% CI) between intervention groups will be estimated using a Cox proportional hazard model with the stratification factors of study site and gender as covariates.

The cumulative incidence functions for the 2 intervention arms will be summarized using Kaplan-Meier method and displayed graphically. The cumulative incidence rate over

time at each scheduled time-points of the protocol together with appropriate 95% confidence interval will be provided.

The time to complete the TMT-A test and the TMT-B test, as well as, the 7-day average of total steps, sitting and lying activity (hours), standing activity (hours) and stepping activity (hours) from ActivPal accelerometry will be summarized by visit using number, median, Q1, Q3, minimum and maximum. In addition, results overtime will be presented graphically using boxplots.

For other efficacy parameters not normally distributed, a non-parametric approach will be used. Descriptive statistics will be summarized using median, Q1, Q3, minimum and maximum.

All secondary endpoints analyses will be provided also in the randomized population with a baseline SPPB  $\geq 8$  assigned by randomization.

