##### **4.3.2. Secondary outcomes**

- a. Changes in physical performance measures
  - Short physical performance battery (SPPB)
  - Handgrip strength
  - Usual gait speed
- b. Changes in disability status
  - Pepper Assessment Tool for Disability (PAT-D)
  - Incidence of persistent mobility disability (operationalised as the failure of completing the 400-metre walk test in two consecutive 6-month visits)
- c. Changes in body composition measures (assessed using Dual Energy X-Ray Absorptiometry, DXA), anthropometric parameters (e.g., body mass index, mid-arm circumference, calf circumference), and nutritional status (Mini Nutritional Assessment-Short Form, MNA-SF)
- d. Changes in cognitive function (assessed using Mini Mental State Examination, MMSE) and mood (i.e., Center for Epidemiological Studies-Depression scale, CES-D)

- e. Incidence of falls (assessed using self-reported questionnaire as well as via a technological device) and injurious falls
- f. Modifications of quality of life (measured using the EuroQoL-5D instrument)
- g. Differences in use of healthcare services (e.g., outpatient clinics, emergency room admissions, hospitalisations, institutionalisations)
- h. Mortality rate

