### **10.2.2. Secondary efficacy endpoints**

For the assessment of secondary efficacy endpoints, specific models will be used for continuous outcomes (e.g., changes in physical performance, nutritional status, functional status, cognitive function, and quality of life). Specifically, changes over time between groups will be assessed by a repeated-measure mixed model with terms for intervention, time, baseline score, baseline score by intervention interaction, and time by intervention interaction. For outcomes such as incidence of falls and mortality rate, the analysis defined for the primary efficacy outcome will be replicated (except for the secondary analysis with competitive risk for the mortality rate). Additional analyses (e.g., subgroup composite endpoint analyses) will be defined in agreement with the Managing Board and the Data Safety Monitoring Board and specified in the statistical analysis plan that will be produced prior to the beginning of the analyses.

Please note that within this section, we have limited the description of the analysis plan to the major SPRINTT hypotheses. Nevertheless, the relevance and amount of the data collected during the project will certainly lead to ancillary and secondary analyses always within the scopes and objectives of SPRINTT. Such secondary plans will be developed after formal approval and validation by the Managing Board of SPRINTT.

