### 1.2.2 Secondary objectives

The secondary objectives are to evaluate the effect of the MCI programme compared with the HALE programme on relevant health-related outcomes, in particular:

- Changes in physical performance measures,
- Changes in disability status,
- Changes in body composition, anthropometric and nutritional measures,
- Changes in cognitive function and mood,
- Incidence of falls and injurious falls
- Modifications of quality of life
- Difference in use of healthcare services
- Difference in mortality

A cost-effectiveness analysis is also planned and will be conducted by a dedicated team within work package 5.

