## 1.6 STATISTICAL MODIFICATIONS MADE IN THE STATISTICAL ANALYSIS PLAN

Not applicable

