    - at the date of last available test (failure or success) or date of death if no persistent mobility disability observed and no more than 9 months between two consecutive visits or between the last available successful test and the death,
    - or at the date of the first test (failure or success) where the following test is observed more than 9 months after the previous test, and no persistent disability is observed.

Notes: The baseline assessment is considered as a successful test in this endpoint definition.

If no post-baseline visit is done, then participants will be censored at the date of randomization visit V1-T0 (or date of randomization if V1 is missing).

- Changes in body composition measures from baseline to Month 24 and Month 36, assessed using DXA (centralized reading):

- $aLM^{BMI}$ , in males and females
  - $aLM$  in kg, in males and females
- Changes in anthropometric parameters from baseline to Month 24 and Month 36, assessed by:
  - Weight in kg, assessed using percent change
  - Body mass index (BMI) in  $kg/m^2$ ,
  - Calf circumference in cm,
  - Waist circumference in cm,
  - Hip circumference in cm,
  - Mid-arm circumference in cm
- Changes in nutritional status from baseline to Month 24 and Month 36 assessed by the Mini Nutritional Assessment-Short Form (MNA-SF) score computed directly in the corresponding e-CRF page (ranging from 0 to 14: a score of 12 or greater indicating satisfactory nutritional status and a score strictly below 8 indicating malnutrition)
- Changes in cognitive function from baseline to Month 24 and Month 36, assessed by the Mini Mental State Examination (MMSE) score computed directly in the corresponding e-CRF page (ranging from 0 to 30: a score of 27 or greater indicating normal cognitive function, between 19 and 24 indicating mild cognitive impairment, between 10 and 18 indicating moderate cognitive impairment and a score of 9 or below indicating severe cognitive impairment)
- Changes in Cumulative Illness Rating Scale (CIRS) from baseline to Month 24 and Month 36, computed directly in the corresponding e-CRF page:
  - Total score (ranging from 0 to 56)
  - Severity index (ranging from 0 to 4)
  - Comorbidity index (ranging from 0 to 14)
- Changes in mood from baseline to Month 24 and Month 36 using the Center for Epidemiological Studies-Depression scale (CES-D):

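### Change in lean mass is modelled only within men and within women, so the SAP plans no overall MCI-versus-HALE estimate and no check of whether the effect differs by sex

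*Combined protocol and SAP*

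**What the plan says.** SAP 1.2.2 lists "Changes in body composition, anthropometric and nutritional measures" among the secondary objectives, as an MCI-versus-HALE comparison with no restriction by sex. Protocol 4.3.1 and 4.3.2 do the same. SAP 2.1.3.2 defines the lean-mass endpoints as change to Months 24 and 36 in aLM and BMI-adjusted aLM from centrally read DXA, each listed for men and women.

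SAP 2.4.4.2 sets out one mixed model for repeated measures (MMRM) for the normally distributed continuous endpoints. Its fixed effects include "the randomization strata of site and gender, the intervention-by-time point interaction", plus baseline and baseline-by-time. For the two lean-mass measures it adds one exception: "the models will be assessed separately for males and females". On output it says "These models will provide adjusted least-squares means estimates at Month 24 and Month 36 for both intervention arms", together with the arm difference, its standard error and a 95% confidence interval.

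Protocol 10.2.2 says of continuous secondary outcomes that "changes over time between groups will be assessed by a repeated-measure mixed model with terms for intervention, time, baseline score", followed by two interaction terms, and mentions no split by sex. SAP 2.4.4.3 makes all secondary efficacy endpoints exploratory.

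**The concern.** An objective about the effect of the intervention on body composition calls for an overall estimate of that effect. For lean mass the plan provides none. It gives one difference in men and one in women, each less precise than a joint estimate, and does not say how to read them together.

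Low muscle mass is part of the definition of the target condition (protocol 5.3 and 5.3.2), and DXA lean mass is the only direct measure of muscle mass among the SAP's efficacy endpoints. If the interval excludes zero in one sex only, the plan offers neither an overall answer nor an interaction estimate to set against the contrast, and emphasis may drift to the sex that looks better. For the primary endpoint the SAP avoids this: its subgroup analyses (SAP 2.4.4.1) take sex-specific effects from one model with a subgroup-by-intervention term, and drop the gender stratification when gender is the subgroup. For lean mass it does neither.

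**Working it through.** **Figures in the plan.** The documents state no power, effect size, SD or sex split for lean mass. The only sizing figure is for the primary endpoint: 4 x (1.960 + 1.036)^2 / (ln 0.75)^2 = 434 events, which agrees with protocol 10.1 and SAP 1.3. It says nothing about lean mass. Randomisation is stratified by gender (SAP 1.1), which balances arms within each sex but does not fix the share of men and women.

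**Precision.** Let f be the share of the analysed data held by one sex, with 1:1 allocation and the same residual SD in both sexes (both sexes' shares are assumed). Relative to the pooled standard error (SE):

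- the SE of the arm difference within that sex is 1/sqrt(f);
- the SE of the difference between the two sex-specific effects is sqrt(1/f + 1/(1-f)).

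| Share of women (assumed) | SE ratio, women | SE ratio, men | SE ratio, women minus men |
|---|---|---|---|
| 0.50 | 1.41 | 1.41 | 2.00 |
| 0.60 | 1.29 | 1.58 | 2.04 |
| 0.65 | 1.24 | 1.69 | 2.10 |
| 0.70 | 1.20 | 1.83 | 2.18 |
| 0.75 | 1.15 | 2.00 | 2.31 |

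One sex always holds half or less of the data, so the ratio in the smaller sex is at least 1/sqrt(0.5) = 1.41 whatever the split.

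**Can the overall effect be recovered?** Men and women are independent samples. With equal SD their information shares are f and 1-f, which sum to 1, so an inverse-variance combination of the two reported differences has the pooled SE. The information is not destroyed; the combination is simply not planned.

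**Conditional illustration of discordant results.** Suppose a pooled two-sided 5% comparison had 80% power and the true effect were equal in both sexes. Neither supposition comes from the documents. Power within a sex is then Phi((1.960 + 0.842) x sqrt(f) - 1.960):

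- 50% women: 0.508 in each sex. At least one interval excludes zero with probability 0.758 and both with 0.258, so exactly one does with 0.758 - 0.258 = 0.500.
- 60% women: 0.583 in women, 0.425 in men; exactly one 0.761 - 0.248 = 0.513.
- 75% women: 0.679 in women, 0.288 in men; exactly one 0.772 - 0.196 = 0.576.

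So, under these suppositions, the two sexes would appear to disagree about half the time with no true difference between them.

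**Sensitivity to the assumed effect.** Take 904 evaluable participants (1205 x 0.75, an assumption that borrows the 25% two-year dropout). At an effect of 0.30 SD, pooled power is 0.995 and per-sex power is 0.616 to 0.974 for shares of 0.25 to 0.75. At 0.15 SD the values are 0.616 and 0.203 to 0.497. Absolute power therefore depends on an effect size the documents do not give; the SE ratios do not.

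**The case against.** The case for leaving the plan alone has real substance.

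- **Reporting by sex has a basis in the documents.** The low-lean-mass cut-offs differ by sex (protocol 5.1.2.2), protocol 5.3.2 treats the measures as sex-specific, and SAP 2.1.1 summarises baseline lean mass by gender. Separate models also let variances, covariances and baseline slopes differ. This stands as a reason to show sex-specific results. It does not explain omitting an overall effect on change, since cut-offs concern levels at entry.
- **The endpoints are exploratory.** No alpha, decision rule or power target attaches to lean mass, so power is the wrong yardstick. This stands and limits the weight of the point. A reader might infer that the trial tests lean mass with some 30-70% power where pooling would give 80%. The documents do not support that: both figures rest on an assumed pooled power and sex split, and they describe power within one sex, not for the overall effect.
- **The estimates can be combined afterwards.** They can, as the working shows. What is missing is pre-specification.
- **The protocol does not forbid the split.** SAP 1.6 declares statistical modifications as "Not applicable", and a reader might infer an undeclared departure from the protocol. Protocol 10.2.2, however, allows specific models for continuous outcomes and does not name body composition among its examples, so that inference goes too far.
- **The gender term left in a one-sex model is harmless.** It is constant within the model and does not alter the arm estimates. This is editorial only.

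Nor is lean mass the trial's only direct measure of sarcopenia: the protocol Summary defines sarcopenia by muscle mass and strength, and handgrip strength is also a secondary endpoint.

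**Conclusion.** The point holds as a gap in the planned estimates. Followed as written, SAP 2.4.4.2 yields no overall MCI-versus-HALE difference in change in aLM or BMI-adjusted aLM, and no planned assessment of whether the effect differs by sex, although the objective has no sex restriction and the SAP pools the sexes for its other MMRM endpoints.

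The SE figures assume equal residual SD, and the 60-75% range for women is an assumption. Unequal SDs would shift them: with an SD of change 1.3 times larger in men and 30% men, the illustrative power becomes 0.254 in men and 0.731 in women instead of 0.335 and 0.650. The lack of an overall estimate depends on none of these assumptions. Type I error control for the primary endpoint is also untouched, so the point is minor.

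**What to change.** In SAP 2.4.4.2, add one pre-specified pooled MMRM for each of aLM and BMI-adjusted aLM, with arm, time, arm-by-time, gender, site, baseline and baseline-by-time, plus baseline-by-gender so that the baseline slope may differ by sex. Report the overall arm difference with its 95% confidence interval at Months 24 and 36.

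Keep the sex-specific differences alongside it. Add an arm-by-gender-by-time interaction (with its lower-order terms) to judge whether they differ, and state that an interval excluding zero in one sex only is not evidence of a difference. Drop the redundant gender term from any single-sex model that is retained.

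The cost is a few lines of SAP text and one more model per measure. The pooled model assumes a common residual covariance across sexes; where that is doubtful, let the covariance differ by sex. No new data are needed and no planned result is lost.
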